7.1.2 Secondary endpoints

The secondary outcome measures include:

- Changes in scores on the LOTCA and GCS at the end of treatment compared to baseline;
- Changes in scores on the MMSE and MoCA at the end of treatment and 90 days post-treatment compared to baseline;
- The percentage of subjects at each level of the GOS-E at the end of treatment and 90 days post-treatment;
- ADL-BI at the end of treatment, 30 days, 60 days, and 90 days.

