**10 Sample size calculation**

Before conducting this study, we conducted a pilot trial: The change values of the total scores on the LOTCA scale at 90 days post-drug cessation compared to baseline for L-oxiracetam and oxiracetam were 26.0 ± 11.8 and 22.8 ± 10.0, respectively. The combined standard deviation (SD) for both groups was 11.0, with α set at 0.05 and 1-β at 0.8. Employing an optimal design with a sample ratio of 1:1, PASS software calculated a sample size of 190 cases for each group.

The change values of the total scores on the LOTCA scale at 90 days post-drug cessation compared to baseline for the L-oxiracetam group and the placebo group were 26.0 ± 11.8 and 20.0 ± 11.4, respectively. The combined SD for both groups was 11.6, with α set at 0.05 and 1-β at 0.8. Employing an optimal design with a sample ratio of 2:1, PASS software calculated a sample size of 204 cases for the L-oxiracetam group and 102 cases for the placebo group.

Considering potential dropouts, we increased the sample size by 15%. Therefore, the sample sizes for the L-oxiracetam group, oxiracetam group, and placebo group were set at 236, 236, and 118, respectively.

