**14 Statistical analysis plan**

SAS 9.4 was used for data analysis independently conducted by a biostatistician unaware of the allocation. Continuous variables will be presented as mean ± SD with a 95% CI for normal distribution and as median (range) for abnormal distribution. Categorical variables will be expressed by numbers and percentages. All hypothesis tests were two-sided with α = 0.05. A P-value ≤ 0.05 indicated statistical significance.

The analysis for the primary outcome was conducted using analysis of covariance (ANCOVA). The least squares means of change from baseline at 3 months in LOTCA scores, as well as the mean differences between groups (L-oxiracetam vs. oxiracetam/ Placebo) and 95% CIs were estimated. Cohen’s d and 95% CI was used to calculate the effect size. For the secondary continuous efficacy outcomes, mean differences with corresponding 95% CIs were also analyzed using ANCOVA. For categorical outcomes of GOS-E, the rate differences and 95% CIs between groups were estimated using the approximate normality method and statistically tested with Fisher's exact probability test. All models were adjusted for age, sex, education, and TBI severity at baseline. Stratified analyses were performed to explore the efficacy of the L-oxiracetam intervention on cognitive function in patients with different age (< 60 vs. 60 + years), sex (male vs. female), education (none vs. Primary vs. Secondary school or Higher), and TBI severity (mild vs. moderate). Moreover, multiplicative interactions were tested by including a cross-product item in the model for the intervention group with age, sex, education, or TBI severity.

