**Attachment 4. Glasgow Outcome Scale Extended (GOS-E)**

**Glasgow Outcome Scale Extended (GOS-E)**

| Score | Characteristic |
| --- | --- |
| 8 | Upper Good Recovery, full recovery or minior symptoms that do not affect daily life |
| 7 | Lower Good Recovery, with minor physical or mental deficits that affects daily life |
| 6 | Upper Moderate Disability, some disabilitiy exists, but can partly resume work or previous activities |
| 5 | Lower Moderate Disability, independent but cannot resume work/ school or previous social activities |
| 4 | Upper Severe Disability, needs partial assistance for daily activities |
| 3 | Lower Severe Disability, needs full assistance for daily activities |
| 2 | Vegetative State, absence of awareness of self and environment |
| 1 | Death |

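### GOS-E, an ordered eight-level secondary endpoint, is analysed by methods that ignore the order, with an interval that under-covers for rare levels against placebo

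*Protocol*

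**What the plan says.** Section 7.1.2 lists as a secondary endpoint: "The percentage of subjects at each level of the GOS-E at the end of treatment and 90 days post-treatment". The scale in Appendix 3, Attachment 4 is ordered. It runs from death (score 1) and score 2 ("Vegetative State, absence of awareness of self and environment") up to score 8 ("Upper Good Recovery, full recovery or minior symptoms that do not affect daily life").

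Section 14 treats GOS-E as categorical. On estimation it says: "For categorical outcomes of GOS-E, the rate differences and 95% CIs between groups were estimated using the approximate normality method". On testing it says: "statistically tested with Fisher's exact probability test". The next sentence reads: "All models were adjusted for age, sex, education, and TBI severity at baseline". The significance level is general: "All hypothesis tests were two-sided with α = 0.05". The section gives no ordinal method, no cut-point for a dichotomy and no multiplicity rule for GOS-E levels.

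The planned arm sizes are in section 10: "the sample sizes for the L-oxiracetam group, oxiracetam group, and placebo group were set at 236, 236, and 118, respectively".

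**The concern.** Three features of the stated method do not fit the endpoint.

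- **Order.** A treatment that moves patients up the scale acts on all levels together. Fisher's test does not see this, and the change at a middle level can point either way while patients improve.
- **Rare levels.** Section 4.2.1 admits stable patients with GCS 10-15 who are not undergoing craniotomy, so the lowest GOS-E levels should hold few patients. Normal-approximation intervals for a difference in proportions are unreliable there. They also come from a different method than the Fisher P-value, so the two can disagree.
- **Adjustment.** The adjustment sentence follows directly on the GOS-E methods, yet neither of them can carry a covariate.

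At stake is whether GOS-E gives one readable treatment effect per visit and contrast, or a set of level differences with low power and, in some cells, wrong intervals.

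**Working it through.** **Inputs.** From the protocol: eight ordered levels (Attachment 4), two visits (7.1.2), two contrasts with L-oxiracetam (14), two-sided 0.05 (14), arms of 236/236/118 (10). The protocol states no GOS-E distribution, effect size or power, so there is no figure to reproduce. Three control distributions for levels 1 to 8 are assumed:

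- A: 0.5 / 0.2 / 1.3 / 4 / 9 / 15 / 30 / 40%
- B: 1 / 0.5 / 3.5 / 10 / 15 / 20 / 25 / 25%
- C: 0.2 / 0.1 / 0.7 / 2 / 5 / 10 / 22 / 60%

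**1. Order.** Permuting the eight level labels leaves every Fisher P-value unchanged, for eight 2x2 tables or for one 2x8 table, so the order plays no part under either reading.

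Power was simulated with 3,000 trials per scenario, 236 vs 118, under a proportional-odds shift: odds of being at or below level k on treatment = control odds / OR. A Wilcoxon test stands in for the unadjusted ordinal analysis, and a 2x8 chi-square for an r x c Fisher test.

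| Distribution | OR | Ordinal | One unordered test |
|---|---|---|---|
| A | 1.0 | 0.054 | 0.042 |
| B | 1.0 | 0.053 | 0.048 |
| C | 1.0 | 0.050 | 0.039 |
| A | 1.5 | 0.483 | 0.292 |
| B | 1.5 | 0.525 | 0.286 |
| C | 1.5 | 0.428 | 0.239 |
| A | 2.0 | 0.913 | 0.726 |
| B | 2.0 | 0.934 | 0.742 |
| C | 2.0 | 0.838 | 0.630 |

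The loss is about 19 to 24 percentage points of power. A separate simulation, also under an assumed distribution, gave 0.49 against 0.30 at OR 1.5 and 0.90 against 0.68 at OR 2.

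A middle level can also mislead. Under A with OR 2, level 7 falls from 30.0% to 25.2% in the arm that does better, because more patients reach level 8 (40.0% to 57.1%).

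**2. Separate tests, if that is what is meant.** With no treatment effect, the simulated chance that at least one of eight Fisher tests reaches 0.05, in one contrast at one visit, is 0.203 (A), 0.239 (B) and 0.170 (C). With Bonferroni correction, power at OR 1.5 is 0.18-0.20.

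**3. Interval coverage.** The interval is d ± 1.96 × sqrt[p1(1−p1)/n1 + p2(1−p2)/n2]. Exact binomial enumeration (L-oxiracetam rate first) gives:

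| Arms | True rates | Coverage |
|---|---|---|
| 236 vs 118 | 2% vs 2% | 0.914 |
| 236 vs 118 | 1% vs 2% | 0.895 |
| 236 vs 118 | 0.5% vs 1.5% | 0.828 |
| 236 vs 118 | 5% vs 5% | 0.942 |
| 236 vs 236 | 1% vs 1% | 0.955 |
| 236 vs 236 | 0.5% vs 1.5% | 0.949 |

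If both arms are empty at a level, the interval is 0 to 0. At a true rate of 0.5% in each arm this has probability 0.995^354 = 0.17 against placebo and 0.995^472 = 0.09 against oxiracetam. At 0.2% the values are 0.998^354 = 0.49 and 0.998^472 = 0.39.

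**4. Interval against P-value, 236 vs 118.**

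- 5 vs 0 events: d = 2.12 points, SE 0.94, interval +0.3 to +4.0, which excludes zero; Fisher P = 0.17.
- 0 vs 3 events: d = −2.54 points, SE 1.45, interval −5.4 to +0.3, which includes zero; Fisher P = 0.036.

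**5. Adjustment.** A crude rate difference and Fisher's test have no covariate term. Either the adjustment sentence is meant for GOS-E and cannot be carried out, or it refers only to the ANCOVA models and GOS-E is unadjusted.

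**The case against.** Much can be said for the plan.

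- **Number of tests.** A reader might infer 32 tests (8 levels × 2 visits × 2 contrasts) and a false-positive chance of about 20% per visit and contrast. Section 14 does not say that Fisher's test is run per level. The endpoint wording suggests it, but one 2x8 test per visit and contrast, four in all, fits the text too and keeps its size (0.039-0.048 in the simulations). This objection stands, so the false-positive figure is conditional.
- **Sparse cells.** A reader might infer that the whole method fails there. Fisher's test does not: its simulated size at levels 1 and 2 is 0.000-0.017, though its power there is at most about 5% even at OR 2. An empty placebo arm alone does not collapse the interval; both arms must be empty. Against oxiracetam, coverage is adequate apart from those zero-width intervals. Against placebo it recovers once a level holds about 5%.
- **Direction.** A difference at level 8 or level 1 does have a clear direction. The ambiguity belongs to the middle levels.
- **Adjustment.** A reader might see a contradiction. If the sentence covers only the ANCOVA models there is none, and an unadjusted comparison in a randomized trial is valid. What remains is unclear wording.
- **Importance.** GOS-E is one of several secondary endpoints, and section 5.8 uses it to assess prognosis. The analysis does match the endpoint as defined, the percentage at each level.

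None of this answers the loss of order, which holds under either reading, or the poor intervals for rare levels against placebo.

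**Conclusion.** The point holds in limited form. The stated GOS-E analysis discards the order of the scale. At 236 vs 118 this costs about 19 to 24 percentage points of power at common odds ratios of 1.5 and 2. The interval is wrong for rare levels in the placebo contrast, with coverage down to 0.828 in the cases examined, and it can disagree with the P-value reported beside it. An error rate of 0.17-0.24 per visit and contrast applies only if the levels are tested separately.

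The power, error-rate and sparsity figures rest on assumed GOS-E distributions and, for power, on a proportional-odds shift. The coverage figures are exact for the rates shown, but those rates are assumed too. The documents do not support saying that 32 tests are planned, that Fisher's test fails, or that the adjustment sentence is certainly a contradiction. The primary LOTCA conclusion is unaffected. This is a change that should be made to a secondary analysis.

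**What to change.** In section 14, make the GOS-E inference one ordinal analysis per visit and contrast: a proportional-odds model with treatment, age, sex, education and TBI severity, reporting the common odds ratio with its 95% CI. Name a Wilcoxon-type estimate as back-up if proportionality is poor. Keep the percentage at each level, as section 7.1.2 defines it, as description. For any rate difference that is reported, use a score-based interval (Newcombe or Miettinen-Nurminen). State which analyses the adjustment sentence covers.

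The cost is revised wording and minor programming, with no new data. The drawback is the proportional-odds assumption, which sparse low levels make hard to check; the rank-based back-up covers this.

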| **Statistical Analyses:**  SAS 9.4 was used for data analysis independently conducted by a biostatistician unaware of the allocation. Continuous variables will be presented as mean ± standard deviation (SD) with a 95% confidence interval (CI) for normal distribution and as median (range) for abnormal distribution. Categorical variables will be expressed by numbers and percentages.  All hypothesis tests were two-sided with α = 0.05. A P-value ≤ 0.05 indicated statistical significance. Analysis followed the intention to treat (ITT) principle, including all randomized cases receiving at least one drug dose. For cases with incomplete treatment process, the last observed data were carried forward to the trial's final results.  When comparing the change values from baseline for each group, an analysis of covariance (ANCOVA) model was used, adjusting for baseline, injury classification, and education level. |
| **Target Sample Size:**  Before conducting this study, we conducted a pilot trial: The change values of the total scores on the LOTCA scale at 90 days post-drug cessation compared to baseline for L-oxiracetam and oxiracetam were 26.0 ± 11.8 and 22.8 ± 10.0, respectively. The combined SD for both groups was 11.0, with α set at 0.05 and 1-β at 0.8. Employing an optimal design with a sample ratio of 1:1, PASS software calculated a sample size of 190 cases for each group.  The change values of the total scores on the LOTCA scale at 90 days post-drug cessation compared to baseline for the L-oxiracetam group and the placebo group were 26.0 ± 11.8 and 20.0 ± 11.4, respectively. The combined SD for both groups was 11.6, with α set at 0.05 and 1-β at 0.8. Employing an optimal design with a sample ratio of 2:1, PASS software calculated a sample size of 204 cases for the L-oxiracetam group and 102 cases for the placebo group.  Considering potential dropouts, we increased the sample size by 15%. Therefore, the sample sizes for the L-oxiracetam group, oxiracetam group, and placebo group were set at 236, 236, and 118, respectively. |
| **Trial Period:**  September 2019- May 2024. |

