**5.11 Screening Period (-72h to 0h)**

During this visitation window, the following tasks need to be completed and documented:

- Obtain written informed consent from the guardian and/ or participant.
- Clinical trial sites to assign screening numbers based on the order in which participant consent forms are signed.
- Researchers collect demographic data, medical history, and medication history, and perform vital signs checks on participants.
- Participants who have not undergone a CT or MRI scan post-injury should have one conducted.
- Collect blood and urine samples from participants to test for routine blood parameters (WBC, RBC, HGB, PLT), routine urine parameters (PRO, GLU, LEU, ERY), liver function (AST, ALT, TBIL, γ-GT, ALP), kidney function (Scr, GFR), coagulation function (PT, APTT, TT, FIB), CK, and TG. Conduct a 12-lead ECG and perform a blood pregnancy test in women of childbearing age. If these tests have been conducted post-injury already, they do not need to be repeated.
- Participants to complete the MMSE and the GCS for scale evaluation.
- Researchers to determine the suitability of participants for the trial based on collected information and test results, in accordance with inclusion and exclusion criteria.
- Participants to complete the MoCA and LOTCA for scale evaluation.
- Randomize participants into groups, assign drug numbers, and dispense treatment drugs.

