**7 Endpoints evaluation criteria**

**7.1 Efficacy** **Endpoints:**

7.1.1 Primary endpoint

- The primary outcome measure is the change in scores on the LOTCA at 90 days post-treatment compared to baseline.

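### The Synopsis and Section 14 give different covariate lists for the primary ANCOVA of LOTCA change, and only the Synopsis list includes a baseline score

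*Protocol*

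**What the plan says.** Section 7.1.1 defines the endpoint: "The primary outcome measure is the change in scores on the LOTCA at 90 days post-treatment compared to baseline". Two places then describe its model.

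- Protocol Synopsis, Statistical Analyses: for changes from baseline, "an analysis of covariance (ANCOVA) model was used, adjusting for baseline, injury classification, and education level".
- Section 14: the primary outcome is analysed by ANCOVA, with least squares means of LOTCA change and differences between groups. After covering the secondary outcomes, the section adds "All models were adjusted for age, sex, education, and TBI severity at baseline".

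Section 5.11 places the baseline measurement before randomisation: "Participants to complete the MoCA and LOTCA for scale evaluation". The Trial Schedule also shows LOTCA at screening.

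**The concern.** An ANCOVA is defined by its covariates. With two lists in one protocol, two programmers working faithfully from it could produce different primary estimates, intervals and p-values. The choice should be closed before anyone can see which list is more favourable.

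The omission from Section 14 also matters in its own right. Change scores usually depend on the starting value, and LOTCA is bounded. The Appendix 3 scoring gives a maximum of 2×8 + 17×4 + 3×5 + 4×4 + 4 = 119, so a patient who starts high has less room to gain. Section 12 describes block randomisation and names no stratification factor, so nothing stated there balances baseline LOTCA by design. A model without it leaves that part of the variation in the residual.

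**Working it through.** **1. The lists side by side.** Injury classification and TBI severity are read as the same factor.

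| Covariate | Synopsis | Section 14 |
|---|---|---|
| Baseline value of the score | yes | no |
| Injury classification / TBI severity | yes | yes |
| Education | yes | yes |
| Age | no | yes |
| Sex | no | yes |

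The words about baseline at the end of the Section 14 sentence describe the listed patient characteristics. None of the four is a LOTCA score.

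**2. The plan's own sample size.** Section 10 gives LOTCA changes "for L-oxiracetam and oxiracetam were 26.0 ± 11.8 and 22.8 ± 10.0, respectively", a difference of 26.0 − 22.8 = 3.2. It uses a combined SD of 11.0, two-sided α of 0.05 and power of 0.80.

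n per group = 2 × (1.960 + 0.842)² × 11.0² / 3.2² ≈ 186

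The plan states 190, within 3% of this. Power at 190 per group is 0.809 (normal approximation) or 0.807 (noncentral t). The SD of 11.0 is that of the change score with no covariate reduction.

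**3. What baseline LOTCA could add.** Let r be the size of the partial correlation of baseline LOTCA with LOTCA change, given the other covariates. The documents give no value, so 0 to 0.7 is assumed. The SD of 11.0 is used for the model without the baseline score; any reduction from the other covariates is ignored. The group size is 204, the Section 10 figure for L-oxiracetam before the dropout allowance, taken for oxiracetam too because allocation is 2:2:1.

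Residual SD = 11.0 × √(1 − r²)

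SE = residual SD × √(2/204)

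Power ≈ Φ(3.2/SE − 1.960)

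| r | SE | Power at 204 per group | n per group for 80% power |
|---|---|---|---|
| 0 | 1.089 | 0.836 | 186 |
| 0.2 | 1.067 | 0.851 | 179 |
| 0.4 | 0.998 | 0.894 | 156 |
| 0.6 | 0.871 | 0.957 | 119 |
| 0.7 | 0.778 | 0.984 | 95 |

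The r = 0 row is also the power of the model without baseline LOTCA. The forgone gain is 0.984 − 0.836 = 0.148 at most over this range.

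For L-oxiracetam against placebo (difference 6.0, SD 11.6, 204 and 102 patients) power is already 0.989 at r = 0, so almost nothing is at stake there.

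**4. How often the two models disagree.** Trials of 204 against 204 were simulated with a true difference of 3.2 and SD 11.0, 4,000 runs for each r. Each was analysed with and without the baseline score.

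| r | Significant without | Significant with | Verdict at 0.05 differs | SD of shift in the estimate |
|---|---|---|---|---|
| 0.2 | 0.837 | 0.843 | 3.6% | 0.22 |
| 0.4 | 0.826 | 0.893 | 9.2% | 0.44 |
| 0.6 | 0.840 | 0.953 | 12.8% | 0.66 |

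The shift is in LOTCA points, against a planned difference of 3.2. The simulation isolates the baseline score; the effect of adding or dropping age and sex is not sized.

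**The case against.** The best defence is that Section 14 specifies a legitimate model. Under randomisation, ANCOVA of change without the baseline score is unbiased for the treatment difference, and subtracting baseline already deals with part of any chance imbalance. A separate statistical analysis plan may settle the list, and the protocol assigns the analysis to a statistician unaware of allocation. All of this stands. It limits the consequence but does not reconcile two statements in the same document: a plan that follows one contradicts the other.

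A reader might infer more than the documents support:

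- **That the trial is underpowered under Section 14.** It is not. The planned number rests on unadjusted change-score SDs, so leaving out the baseline score forgoes a gain without taking power below 80%.
- **That 15% to 35% of the sample is wasted.** This comes from the variance ratio (1 + r)/2, with r here the correlation of baseline with Day 90: 0.65, 0.75 and 0.85 at r = 0.3, 0.5 and 0.7. The comparator in that ratio is a change score with no covariates, whereas Section 14 has four, which may share information with baseline LOTCA. The ratio also assumes equal variances at both times, which a bounded scale makes doubtful.
- **That baseline LOTCA is the strongest covariate available.** That is a usual expectation, but no figure in the protocol shows it.
- **That the protocol permits a choice of model after unblinding.** It does not say so. The ambiguity leaves that risk open, and no more.

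**Conclusion.** The contradiction is certain from the text: two covariate lists for one primary ANCOVA, no rule of precedence, and the baseline score in only one of them. The primary model should be settled before unblinding.

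The size depends on a correlation that the documents do not report. For an assumed partial correlation of 0 to 0.7, the Section 14 list forgoes 0 to about 15 power points for L-oxiracetam against oxiracetam. At 0.2 to 0.6, the presence or absence of the baseline score changes the significance verdict in about 4% to 13% of trials at the planned effect. These figures rest on the planned difference of 3.2, the SD of 11.0 and 204 analysed patients per group. The loss is one of precision and clarity, not of validity.

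**What to change.** State one model in both the Synopsis and Section 14, fixed before unblinding:

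- **Primary:** LOTCA change = treatment + baseline LOTCA + TBI severity + education, plus age and sex if they are kept.
- **MMSE, MoCA and GCS change:** the same model with the baseline of the same scale.
- **ADL-BI:** the Trial Schedule has no baseline assessment, so use the remaining covariates.
- **GOS-E:** limit the Section 14 adjustment sentence to the ANCOVA and other regression models. The rate difference and Fisher's exact test named there take no covariates.

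The cost is a wording change through the Section 18 procedure: a documented amendment signed by the principal investigator, approved by the ethics committee and acknowledged by the sponsor. No new data are needed. The stated trial period runs to May 2024, so if results have already been seen, the change needs a dated justification.
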